## 8.2 Secondary study parameters

EGM thresholds and the MTPRT will be reported preoperatively and 1 week, 6 weeks and 6 months postoperatively. The total score and scores of different categories of the questionnaires will be reported preoperatively and 1 week, 6 weeks, 3 months and 6 months postoperatively. The odour identification score will be reported preoperatively and 1 week postoperatively. Mean (or median) and standard deviation (or the range) will be reported. Differences between the different groups of CTN injury will be analysed using linear regression analysis.

Postoperative symptoms of taste disturbance will be analysed using logistic regression analysis, as these outcomes will be presented dichotomously.

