### 6.1.2 Secondary study parameters

- The difference between the preoperative and postoperative EGM thresholds in uA for different locations of the tongue
- The difference between the preoperative and postoperative amount of identified sweet taste strips of the ipsilateral tongue of the operated ear
- The difference between the preoperative and postoperative amount of identified salty taste strips of the ipsilateral tongue of the operated ear
- The difference between the preoperative and postoperative amount of identified sour taste strips of the ipsilateral tongue of the operated ear
- The difference between the preoperative and postoperative amount of identified bitter taste strips of the ipsilateral tongue of the operated ear
- The difference between the preoperative and postoperative amount of identified umami taste strips of the ipsilateral tongue of the operated ear
- The postoperative existence of metallic taste sensation
- The postoperative existence of dryness of the mouth
- The postoperative existence of tingling sensations of the tongue
- The postoperative existence of numbness of the tongue
- The difference between the preoperative and postoperative score of the AHSP questionnaire
- The difference between the preoperative and postoperative score of the health-related quality of life questionnaire
- The difference between the preoperative and postoperative total and sub scores of the MTPRT
- The difference between the preoperative and postoperative odour identification score

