## 6.2 Randomisation, blinding and treatment allocation

There will be no randomization. The patient and outcome assessor are blinded to the predictor variables, including the presence or absence of CTN injury. The surgeon will complete an electronic Case Report Form (eCRF) in Castor, including the predictor variable CTNinjury. Both patients and researchers will not be informed about the CTN injury until the patient has finished all evaluations. The eCRF will be locked to read for the researchers and the surgeon will not report the CTN injury in the surgery report. After a patient has completed all evaluations, the investigator will read the eCRF and report the CTN injury in the electronic patient record. We do not expect that there are circumstances that require us to unblind the patient or the outcome assessor during the study.

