## 8.1 Primary study parameter

The primary study parameter is the change in the amount of identified taste strips by patient, preoperatively and 6-8 weeks postoperatively. This outcome will be presented continuous with a range from 1 to 20 identified taste strips. Mean (or the median) and standard deviation (or the range) will be reported. The effect of CTN injury on the amount of identified taste strips will be evaluated using linear regression analysis. The following confounding variables will be included in the analysis: age, gender, smoking, weight, gastroesophageal reflux, olfactory dysfunction, salivary hypofunction, medication, rhinosinusitis/allergic rhinitis, previous COVID-19 and diabetes mellitus (12–22).

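### Section 8.2 gives the secondary comparisons of non-randomised nerve-injury groups no adjustment set and no named visit, and the four symptom endpoints ignore whether the symptom was present before surgery

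*Protocol*

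**What the plan says.** Section 6.2 of the Protocol states: "There will be no randomization". The surgeon records the injury, and section 3 gives it three categories.

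For the primary outcome, section 8.1 names an adjustment set: "The following confounding variables will be included in the analysis: age, gender, smoking, weight, gastroesophageal reflux, olfactory dysfunction, salivary hypofunction, medication". The list goes on to nasal disease, earlier COVID-19 and diabetes, eleven confounders in all.

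Section 8.2 covers the secondary outcomes:
- Electrogustometer (EGM) thresholds and the food-preference task (MTPRT): "EGM thresholds and the MTPRT will be reported preoperatively and 1 week, 6 weeks and 6 months postoperatively".
- Scores of the "questionnaires will be reported preoperatively and 1 week, 6 weeks, 3 months and 6 months postoperatively".
- Odour: "The odour identification score will be reported preoperatively and 1 week postoperatively".
- Continuous outcomes: "Differences between the different groups of CTN injury will be analysed using linear regression analysis".
- Symptoms: "Postoperative symptoms of taste disturbance will be analysed using logistic regression analysis, as these outcomes will be presented dichotomously".

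Section 8.2 names no covariates, no visit for comparison and no method for repeated values.

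Section 6.1.2 defines the continuous secondary outcomes as differences between before and after surgery. The four symptoms (metallic taste, dry mouth, tingling, numbness) are defined by the later state alone, for example: "The postoperative existence of dryness of the mouth". Under section 6.3 the questionnaires are also completed once before surgery.

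**The concern.** Three things follow if the text is carried out literally.

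- **Confounding.** The injury groups arise during surgery and may differ in age and health for every outcome, not only the primary one. The Introduction links younger age to better recovery and faults earlier studies for disregarding age. Every objective in section 2 that sets stretching against sacrificing is a secondary one, so these analyses carry a question that motivates the study.
- **Symptoms.** A patient whose mouth was dry before surgery and stays dry counts as a postoperative case. This dilutes the contrast if such patients are spread evenly over the groups, and biases it if they are not.
- **Visits.** With three or four postoperative times and none designated, the analyst must choose between pooling visits, fitting each one, or picking one. The choice affects the error rate, and leaving it open permits selection after the results are seen.

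**Working it through.** **The plan's own figure.** Section 4.4 allows 10 patients for each of 14 degrees of freedom: 14 x 10 = 140, plus 14 for withdrawal = 154. This reproduces. It concerns the primary model only; no figure is given for the secondary analyses.

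**Inputs.** The number of postoperative times m is 3 (EGM, MTPRT) or 4 (questionnaires), from section 8.2. Two-sided alpha of 0.05 and a within-patient correlation rho of 0.3-0.7, equal between visits, are assumptions; the protocol gives neither. For change scores that share one preoperative value, equal variances and equal pairwise correlation r give a correlation of (1 - r) / [2(1 - r)] = 0.5, the middle of that range.

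**Reading A: visits pooled as independent rows.** The injury group is fixed within a patient, so the design effect is DE = 1 + (m - 1)rho. The reported standard error is 1/sqrt(DE) of its true size, and the true type I error is 2[1 - Phi(1.96/sqrt(DE))].

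| m | rho | DE | SE ratio | Type I error |
|---|---|---|---|---|
| 3 | 0.3 | 1.6 | 0.79 | 0.121 |
| 3 | 0.5 | 2.0 | 0.71 | 0.166 |
| 3 | 0.7 | 2.4 | 0.65 | 0.206 |
| 4 | 0.3 | 1.9 | 0.73 | 0.155 |
| 4 | 0.5 | 2.5 | 0.63 | 0.215 |
| 4 | 0.7 | 3.1 | 0.57 | 0.266 |

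**Reading B: one regression per visit.** Each test keeps its level. A simulation with 140 patients in two equal groups, m = 4 and rho = 0.5 gave 0.050 for a single visit, against 0.216 when pooled. The cost lies elsewhere:
- *Multiplicity.* If the tests were independent, the chance of at least one false positive per outcome would be 1 - 0.95^3 = 0.143 or 1 - 0.95^4 = 0.185. With test correlations of 0.3-0.7, simulation gives 0.136-0.110 for three visits and 0.174-0.130 for four.
- *Efficiency.* For an effect constant over visits, a correlated-data model that averages m visits has DE/m of the single-visit variance: 0.53-0.80 for m = 3 and 0.48-0.78 for m = 4.
- *Number of fits.* Section 6.1.2 lists 14 parameters. EGM 3, five taste qualities 5 x 3 = 15 (section 5.1), four symptoms 4 x 4 = 16 (assuming all four times), two questionnaires 2 x 4 = 8, MTPRT 3 and odour 1 add up to 46, before EGM sites and MTPRT sub-scores.

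**Can the 8.1 list simply be copied?** Not for every outcome.
- Olfactory dysfunction largely duplicates the preoperative odour score when odour is the outcome.
- The Introduction says the nerve also supplies salivary glands, so salivary function measured after surgery may be a result of the injury. Only preoperative values can serve as confounders.
- For a symptom, the limit is the smaller of the symptomatic and symptom-free groups, at most 70 of 140. The protocol's own allowance of ten per degree of freedom then permits at most 70/10 = 7, not 14.

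**Symptoms.** Set side by side, section 6.1.2 uses the preoperative value for every continuous secondary outcome and for none of the four symptoms. No size can be given, because the documents do not state how common these symptoms are before surgery.

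**The case against.** The strongest reply is that section 8.2 is silent on covariates and does not prescribe an unadjusted analysis. An analysis plan, which section 10.1 mentions, may carry the 8.1 list over. That stands against saying that the comparisons are confounded. It does not remove the contrast between two adjacent sections, one with a named set and one without, and the set could not be copied unchanged.

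A reader might infer that the planned standard errors are wrong. The documents do not support this. Section 8.2 reports by time point and section 6.1.2 uses pre-to-post differences, so one fit per visit is the natural reading, and each such fit is valid. The change scores already use the within-patient pairing, and the odour score has a single postoperative time, so the repeated-measures point does not touch it.

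On symptoms, the exclusion criteria remove patients with a history of orofacial pain or dysesthesia, or with diseased oral mucosa, so less tingling and numbness should pre-exist. Dry mouth and metallic taste are not excluded by name. Salivary hypofunction is a listed confounder, but for the primary model only. Section 6.3 does not itemise the four symptoms in the questionnaires, so their preoperative recording is likely but not shown. That caveat stands and needs checking.

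**Conclusion.** The point holds in a limited form.

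- **Firmest:** the four symptom endpoints leave out preoperative status. This is written into their definition and is not merely left unsaid.
- **Next:** section 8.2 names models for a non-randomised exposure without an adjustment set. Run as written, the comparisons would be open to confounding. Its size cannot be computed, because the documents give no covariate distribution by injury group.
- **Repeated visits:** on the natural reading the cost is efficiency and multiplicity, with an 11-17% chance of at least one false positive per outcome. The 12-27% error rate applies only to pooled rows. Both ranges rest on the assumed correlations.

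The primary analysis at its single visit and the sample size of 154 are unaffected. The change should be made before any outcome data are analysed by injury group.

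**What to change.** Amend section 8.2, and the symptom definitions in 6.1.2, as follows.

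- **Continuous outcomes with repeated postoperative visits** (EGM, taste qualities, MTPRT, questionnaires): one linear mixed model per outcome with injury, visit, injury x visit, the preoperative value and confounders measured before surgery, and a patient random effect. Add tongue site for EGM. Report the injury contrast at each visit. With the preoperative value as a covariate, this contrast is the same whether the response is the postoperative value or the change.
- **Odour score:** linear regression at the single postoperative time, adjusted for the preoperative score and the confounders, leaving out olfactory dysfunction as redundant.
- **Symptoms:** a GEE or mixed logistic model adjusted for preoperative presence of the symptom and a short set such as age and type of operation. The latter is not in the 8.1 list, but the study combines two operations and injury types may be distributed differently between them. Injury (2 df), preoperative presence, age and operation make 5 df, which on the protocol's allowance calls for 50 patients in the smaller outcome group.
- **Check** that the four symptoms are asked about at the preoperative session; if not, add them.

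The cost is wording and modest extra programming, and the named software version should be confirmed to fit these models. No visits are added. The main drawback is that the symptom models can carry few covariates, so some confounding will remain there.

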## 8.3 Other study parameters

Baseline characteristics will be presented in medians and averages.

## 8.4 Interim analysis

No interim analyses will be performed.

# 9. ETHICAL CONSIDERATIONS

## 9.1 Regulation statement

The study will be conducted according to the principles of the Declaration of Helsinki (WMA Declaration of Helsinki – Ethical Principles for Medical Research Involving Human Subjects. 64^th^ WMA General Assembly, Fortaleza, Brazil, October 2013) and in accordance with the Medical Research Involving Human Subjects Act (WMO, the ‘gedragscode gezondheidsonderzoek’.

## 9.2 Recruitment and consent

Patients will be recruited from the outpatient ENT department of the UMCU. Patients will be asked to participate in the study after the decision has been made that non inflammatory surgery of the middle ear, like cochlear implant surgery or surgery of the ossicles is needed. The treating physician will provide the patient with the information letter and informed consent form and will ask the patient for permission to be contacted by the research team. Patients will be contacted by the researcher after at least one week to answer potential questions. The next visit to the UMCU the patient can bring the IC form where it can be signed together with the investigator. In most cases, the IC form will be signed after the preoperative visit to the treating physician. The treating physician is not present when signing the IC form. The patient will receive a copy of the signed IC. The informed consent will also documented in Hix. If the patient will sign the IC form, the patient will receive the first test session at the same day. If a patient does not want to participate, contact with the investigator will be terminated.

## 9.3 Objection by minors or incapacitated subjects

If a patient does not want to receive the EGM or the TST, the patient will not be forced. The patient will be excluded from the study. Only competent patients 18 years of age or older will be included in our study.

## 9.4 Benefits and risks assessment, group relatedness

Patients will not have a direct benefit of this study, but with these results of the study there will be more scientific knowledge about de postoperative taste function after primary stapes surgery or primary cochlear implantation.

The study burden is moderate. All patients will receive the tests, in the context of the study, during the regular visits to the Department of Otorhinolaryngology. The combination of the fulfilment of the questionnaires and receiving the EGM, the TST and the MTPRT the olfactory test with Sniffin’ sticks will take 1.5 hour. All patients will undergo these tests for 4 times. Except for the sniffin stick test, this will only be done twice. Patient will also complete the questionnaires at home three months after surgery, which will take 30 minutes. The expected total burden due to participation for all patients is likely to be 6.5 hours.

The EGM, TST and the olfactory test are considered as non-risk investigations.

## 9.5 Compensation for injury

The sponsor/investigator has liability insurance which is in accordance with article 7 of the WMO.

The sponsor (also) has an insurance which is in accordance with the legal requirements in the Netherlands (article 7 WMO). This insurance provides cover for damage to research subjects through injury or death caused by the study. The insurance applies to the damage that becomes apparent during the study or within 4 years after the end of the study.

## 9.6 Incentives

Not applicable.

# 10. ADMINISTRATIVE ASPECTS, MONITORING AND PUBLICATION

## 10.1 Handling and storage of data and documents

Data handling and protection is conducted according to the ISO 27001 compliant processes and ICH-GCP and applicable regulations. Confidentiality will be maintained at all times, participant information will not be disclosed to third parties. For this prospective study, only eligible patients admitted or with an appointment at the ENT department will be asked by their treating physician to participate. Direct identifiable—personal data from these patients will be recorded in an Excel file and stored in a secure research folder from the TACO study on the UMC Utrecht network drive. This is for an overview of which patients are asked to participate.

After given informed consent, patients will also be registered in our electronic health record (EHR, HiX). The original signed informed consent forms will be kept in a binder in a locked closet in a locked room at the ENT department. Subsequently, the patient will receive a unique identifier, after which members of the research team will extract all necessary clinical parameters from the electronic health records (EHRs; HiX) into an electronic Case Report Form (eCRF) the UMCU endorsed system Castor EDC. Castor EDC is a browser-based, metadata-driven EDC software solution and workflow methodology for building and managing online databases. The eCRF contains data items as specified in this research protocol. Modification of the eCRF will be made only if deemed necessary and in accordance with an amendment to the research protocol. Access to the eCRF is password protected and specific roles are assigned (e.g. study coordinator, investigator, monitor, etc.).

Only research members directly involved in this study will get access to the all of the collected in Castor. The clinical database will be supplemented with the outcome of three questionnaires (please see paragraph 7.3 Study Procedures). At the end of the study, all generated (meta)data will be stored as a proprietary format (.sav / .xlsx format) in a secure Research Folder Structure with access control. Only members of the research team who are directly involved in the study are allowed to access the key-linking table to enable patient re-identification (only for UMCU patients). In order to reproduce the study findings and to help future users to understand and reuse the (meta)data, all changes made to the raw data, including analysis steps will be documented in an analysis plan. Thus the secure research folder will serve at the end of the study as a data package. The data package will be locally archived on the secured research network disc of the division for 15 years after the study has ended. More details, including the state of FAIRness, can be found in our datamanagement plan on [https://dmponline.dcc.ac.uk/plans/71095](https://dmponline.dcc.ac.uk/plans/__.).

## 10.2 Monitoring and Quality Assurance

Our datamanagement plan can be found on [https://dmponline.dcc.ac.uk/plans/71095](https://dmponline.dcc.ac.uk/plans/__.). See the attached monitor plan.

## 10.3 Amendments

Amendments are changes made to the research after a favourable opinion by the accredited METC has been given. All amendments will be notified to the METC that gave a favourable opinion.

## 10.4 Annual progress report

The sponsor/investigator will submit a summary of the progress of the study to the accredited METC once a year. Information will be provided: the date of inclusion of the first subject, numbers of subjects included and numbers of subjects that have completed the study, serious adverse events/serious adverse reactions, other problems, and amendments.

## 10.5 Temporary halt and (prematurely) end of study report

The investigator will notify the accredited METC of the end of the study within a period of 8 weeks. The end of the study is defined as the last patient’s last visit to the UMCU.

The sponsor will notify the METC immediately of a temporary halt of the study, including the reason of such an action.

In case the study is ended prematurely, the sponsor will notify the accredited METC within 15 days, including the reasons for the premature termination.

Within one year after the end of the study, the investigator/sponsor will submit a final sturdy report with the results of the study, including any publications/abstracts of the study, to the accredited METC.

## 10.6 Public disclosure and publications policy

The data of this research will be used for publication in peer-reviewed international journals. Both positive and negative study results will be disclosed. If the journals do not consider our results for publication, the research will be disclosed through study registers, websites or databases.

# 11. STRUCTURED RISK ANALYSIS

## 11.1 Potential issues of concern

Not applicable.

## 11.2 Synthesis

## No potential risks are described in the literature. The EGM is CE marked and will be used within de indication. The EGM doesn’t connect to any outside voltage source and uses a series of AA batteries to produce it’s stimuli. In addition, the amount of current is confined to very low uA levels that are detected primarily by taste afferents. By using a dual electrode, no current flows through the body. Patients with a pacemaker could therefore be included in the study, but as a precaution we will exclude these patients. The EGM manual describes the precautions for proper use of the EGM (see appendix 1).

